### 2.6 Safety outcomes

Safety outcomes will assess hypotension, hypertension, bradycardia, tachycardia, arrhythmia, interventions for hemodynamic events, headache, dizziness, nausea, vomiting, local skin allergy, wound infection, and toxic reactions.

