### 2.8 Study interventions

In this study, patients will apply an LP5 or placebo patch for 12 h daily on the day before surgery and on postoperative days 1, 2, and 3. The preoperative patch will cover the anticipated incision site, while the postoperative patches will be applied 1.5 cm from either side of the incision. The placebo group will apply a placebo patch, identical in appearance and packaging to the actual medication patch. The lidocaine patches and placebo patches used in this study will be manufactured by Beijing Tide Pharmaceutical Co., Ltd. To maintain blinding, both patients and researchers will remain unaware of group assignments. The patches will be applied by medical professionals who are not involved in patient recruitment or data collection. Randomization will be performed before the study begins by an independent researcher using a computer-generated table of random numbers. Group assignments will be sealed in opaque envelopes to maintain blinding of the investigators, patients, and data analysts, and these envelopes will only be opened after the study is completed. The schedule of patient enrolment, study interventions, and outcome assessments will follow the SPIRIT statement (Table 1). All surgeries will be performed by experienced surgeons who have conducted at least 300 knee arthroplasty procedures prior to the study.

**TABLE 1 T1:** Schedule of patient enrolment, study interventions and outcome assessment.

Time point	Study period								
	Enrolment	Allocation	Post-allocation					Close-out	Follow-up
	Pre-op visit	Pre-op 1 day	Intraoperatively	PACU	24 h post-op	48 h post-op	72 h post-op	Discharged	3 months
Patient enrolment									
Eligibility criteria	×								
Written informed consent	×								
Demographic data	×								
Baseline characteristics	×								
HADS	×								
PCS	×								
Randomization/allocation		×							
Study interventions									
5% Lidocaine Patch		×			×	×	×		
Placebo Patch		×			×	×	×		
Outcome assessment									
WOMAC-Pain Scale	×								×
WOMAC-Stiffness Scale	×								×
WOMAC-Function Scale	×								×
WOMAC-Total Scale	×								×
LANSS									×
SF-36									×
Post-op pain scores					×	×	×		
VAS Sleep score					×	×	×		
Post-op sufentanil use							×		
Need for rescue analgesia							×		
Length of PACU stay				×					
Length of hospital stay								×	
90-day mortality									×
Adverse Events									
Hypotension			×	×	×	×	×		
Hypertension			×	×	×	×	×		
Bradycardia			×	×	×	×	×		
Tachycardia			×	×	×	×	×		

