Arrhythmia			×	×	×	×	×		
HD Events Intervention			×	×	×	×	×		
Headache		×			×	×	×		
Dizziness		×			×	×	×		
Nausea and vomiting		×		×	×	×	×		
Local skin allergy		×			×	×	×		
Wound infection					×	×	×		
Toxic reaction		×			×	×	×		

According to SPIRIT, statement of defining standard protocol items for clinical trials.

HADS, hospital anxiety and depression scale; PCS, pain catastrophizing scale; WOMAC, Western Ontario and McMaster Universities Osteoarthritis Index; LANSS, leeds assessment of neuropathic symptoms and signs; SF-36, Short Form Health Survey; Pre-op, Preoperative; Post-op, Postoperative; VAS, visual analogue scale; PACU, post-anaesthesia care unit; HD, haemodynamic; h, hours; SPIRIT, Standard Protocol Items: Recommendations for Interventional Trials.

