Given the high incidence and refractory nature of CPSP following knee arthroplasty (Beswick et al., 2012), this study aims to test the hypothesis that LP5 can prevent CPSP in patients undergoing knee arthroplasty. This rigorously designed study will evaluate the potential efficacy of lidocaine patches in managing postoperative pain, with a particular focus on their ability to prevent the transition from acute to chronic pain. Through this randomized controlled trial (RCT), we aim not only to provide critical data on the clinical application of lidocaine patches but also to offer new insights for improving future pain management strategies.

This study has several limitations. First, the choice of a 1.5 cm patch distance was based on safety considerations from previous studies and preliminary experiments. Although this distance is considered the safest for orthopedic surgeries, it may not be the optimal distance for analgesic efficacy. Nevertheless, safety is paramount in all clinical treatments. Second, the follow-up period of 3 months may not be sufficient to fully assess the long-term impact of CPSP. We plan to establish a specialized patient cohort for long-term follow-up and further research in this patient population. Additionally, the exclusion of certain patient groups, such as those with long-term opioid use and a history of alcoholism, may limit the generalizability and external validity of the findings. Including these patients in future research is important to provide a more comprehensive understanding of postoperative chronic pain, though their inclusion might introduce significant bias regarding CPSP outcomes.

The primary aim of this randomized controlled trial is to evaluate the effectiveness of the LP5 in preventing CPSP following knee arthroplasty. LP5 will be applied during the early perioperative period, including the day before surgery and postoperative days 1–3. The findings are expected to demonstrate that the use of LP5 may effectively prevent CPSP, reduce acute postoperative pain, and decrease opioid consumption. Additionally, LP5 may facilitate faster postoperative recovery, improving overall patient rehabilitation and quality of life. This study is expected to provide valuable insights for future multimodal analgesia strategies, optimizing postoperative pain management and improving patient outcomes.

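### Scheduled collection of wound infection, skin allergy and toxic reaction stops at 72 h, so later non-serious events are not recorded in either arm

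*Protocol article*

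**What the plan says.** Section 2.6 of the protocol article ends its list of safety outcomes with "local skin allergy, wound infection, and toxic reactions" and gives no period of observation. The only place that fixes one is Table 1 in section 2.8.

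- The row "Wound infection" is marked at 24, 48 and 72 h post-op.
- The row "Local skin allergy" and the toxic reaction row are marked on the day before surgery and at 24, 48 and 72 h.
- No adverse-event row has a mark under discharge or 3 months.

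Section 2.8 has patches worn "for 12 h daily on the day before surgery and on postoperative days 1, 2, and 3", and states that "the postoperative patches will be applied 1.5 cm from either side of the incision". In Table 1 the row "5% Lidocaine Patch" and its placebo counterpart carry their last mark in the 72 h column.

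Section 2.4 provides a telephone or in-person interview at 3 months for the primary outcome. Table 1 also places the other WOMAC scales, LANSS, SF-36 and mortality there. Section 2.10 requires serious adverse events to be reported, whether or not they are related to treatment, and gives no end date for this.

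**The concern.** Three outcomes that bear directly on the local safety of a patch beside a fresh incision stop being collected in the same column in which the last patch appears. Two kinds of event then have no scheduled route into the data unless they are serious: a wound infection that arises after 72 h, and a skin or toxic reaction to the last patch that shows itself after the day-3 check.

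This matters because the Abstract promises evidence on safety as well as efficacy, and the Discussion says that "the choice of a 1.5 cm patch distance was based on safety considerations". A short or empty infection row could be reported as reassurance about wounds in general, when it describes only the first three days. The limitations in the Discussion question the length of follow-up for chronic pain, but not for safety.

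**Working it through.** The plan gives no figure to reproduce here. The check sets the Table 1 rows against the patch schedule.

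**Step 1. Checks by column.**

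| Item | Day before surgery | 24 h | 48 h | 72 h | Discharge | 3 months |
|---|---|---|---|---|---|---|
| Patch (either arm) | × | × | × | × | | |
| Wound infection | | × | × | × | | |
| Skin allergy | × | × | × | × | | |
| Toxic reaction | × | × | × | × | | |

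Skin allergy and toxic reaction are therefore checked in each of the four patch columns. Wound infection is checked in all three of the early postoperative columns. None of the three is checked later.

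**Step 2. Checks after each postoperative patch is removed.** The wear time of 12 h is from section 2.8. The article gives no clock times, so assume first that each patch goes on at its Table 1 time point.

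- On at 24 h, off at 24 + 12 = 36 h: later checks at 48 and 72 h.
- On at 48 h, off at 48 + 12 = 60 h: later check at 72 h.
- On at 72 h, off at 72 + 12 = 84 h: no later check.

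The preoperative patch is followed by the 24, 48 and 72 h checks. So 3 of 4 applications have at least one scheduled check after removal, and the last has none. If instead the 72 h check falls late on day 3, after removal, the last patch has a same-day check and nothing beyond it. Under either reading, a reaction that appears after the day-3 check is not scheduled for collection.

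**Step 3. Share of follow-up covered for wound infection.** With follow-up of 3 months taken as 90 days, 72 h / (90 × 24 h) = 72 / 2160 = 0.033, or about 3%. This is a share of calendar time. It does not say what share of infections would be missed, and the article gives no infection rate or time of onset from which to work that out.

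**Step 4. Other routes into the data.** The reporting rule in section 2.10 has no end date, so a late infection or reaction that is serious can be captured in both arms. Nothing in the article schedules a check for a later event that is not serious. In Table 1 the discharge column carries only length of hospital stay. The 3-month column carries patient interviews but no local safety item.

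**The case against.** Much can be said for the plan. Skin allergy and toxic reaction are looked for in every patch column, and three of the four patches also have a check after removal. The article does not say whether the 72 h check comes before, during or after the last 12 h of wear. Serious late infections have an open-ended reporting route. An article may also leave detailed adverse-event follow-up to the full protocol. The first three of these points stand, and they narrow the concern to non-serious late events. The fourth carries less weight: the schedule is printed in full, has columns for both later time points, and leaves them empty for every adverse event.

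Three stronger readings are tempting, and the document does not support them.

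- *Local safety is hardly observed at all.* For skin and toxic reactions this is contradicted by the marks in Table 1.
- *Most infections would be missed, so the result is bound to be zero in both arms.* The article gives neither an infection rate nor a time of onset, so this cannot be shown from it. The point does not need it: whatever the timing, a non-serious infection after 72 h has no scheduled way into the data.
- *The weakness can be sized by the bound for zero events in 64 patients.* That bound is 1 − 0.05^(1/64) = 4.6% one-sided, or 1 − 0.025^(1/64) = 5.6% as the upper end of a two-sided 95% interval. Both come from the number of patients, and zero events over 90 days would give the same figures. The window limits only the period to which such a bound applies.

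It would also go too far to say that patients are already assessed at discharge, since only an administrative item is recorded there.

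**Conclusion.** The concern holds in a limited form. As Table 1 stands, non-serious wound infection after 72 h and non-serious local reactions to the last patch that appear after the day-3 check are not collected in either arm. An infection count from this schedule describes about 3 of 90 days and cannot support a general statement on wound safety. The conclusion rests on reading Table 1 as the complete schedule and on section 2.10 covering serious events only. It does not depend on when the 72 h check falls relative to the last patch. The primary outcome and its analysis are unaffected; this is an inexpensive improvement to the safety evidence.

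**What to change.** 1. Extend the wound infection and skin reaction rows of Table 1 to the 3-month contact, with a question on any wound infection or skin reaction since surgery.
2. Add one check of skin and toxic reactions after the last patch has been removed, for example at discharge, and state in Table 1 that it follows removal.
3. State the observation period for these outcomes in section 2.6, and report wound-infection risk per arm to 3 months with a confidence interval.

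The 3-month part costs a few case report form items at an interview that already takes place. The discharge part is a small new assessment, because that column now holds only length of stay. The downside is that the 3-month answers will partly be patient-reported by telephone, which the report should say. No change to the patches or their schedule is involved.

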### 2.7 Randomization and blinding

An independent researcher will generate random numbers using an online tool (https://www.sealedenvelope.com/simple-randomiser/v1/lists) with a 1:1 allocation ratio, stratified by center. Randomization results will be stored in sealed opaque envelopes. Patients will be assigned to either the LP5 group or the placebo group. Postoperative care providers will prepare 5% lidocaine and placebo patches with patient numbers marked on the outer packaging. Patients, surgeons, anesthesia providers, outcome assessors, and statisticians will be blinded to group allocation.

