### 2.9 Anaesthetic care

Intraoperative monitoring will include non-invasive blood pressure (NIBP), electrocardiography (ECG), pulse oximetry (SpO_2_), radial artery blood pressure, and nasopharyngeal temperature. Anesthesia will be induced with an intravenous injection of propofol at 1.5–2.5 mg/kg, combined with sufentanil at 0.2–0.4 μg/kg for analgesia. This will be followed by an intravenous injection of rocuronium at 0.6–0.9 mg/kg to achieve muscle relaxation. After induction, an endotracheal tube will be inserted, and its placement will be confirmed. The patients will receive mechanical ventilation, maintaining end-tidal carbon dioxide between 35 and 45 mmHg. Hypotension (mean arterial pressure <65 mmHg or a decrease of 20% from baseline) and bradycardia (heart rate <50 beats/min) will be treated as needed. A thermal blanket will be used during the operation to maintain nasopharyngeal temperature above 36°C. Additional doses of rocuronium will be administered as necessary to maintain muscle relaxation throughout the procedure. Continuous monitoring will include ECG, NIBP, SpO_2_, and bispectral index (BIS), with BIS values maintained between 40 and 60. Both groups of patients received 50 mg of flurbiprofen axetil during surgery. Postoperatively, all patients were transferred to the PACU. During their stay in the PACU and hospitalization, if a patient reported pain with an NRS score of 4 or higher, 5 μg of sufentanil was administered for analgesia, and the total dosage was recorded.

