### 2.14 Principles and methods of unblinding or breaking the blind unblinding timeline

All participants will be unblinded following the completion of the study, specifically after all subjects have completed the 3-month follow-up period. Unblinding Method: The unblinding process will be overseen by an independent DMC. The DMC will oversee and retain all data related to randomization until the designated time for unblinding.

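### Patch preparation is given to postoperative care providers, who are not listed as blinded, and sections 2.7, 2.8 and 2.14 conflict on who holds the allocation during the trial

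*Protocol article*

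**What the plan says.** Section 2.7 has an independent researcher generate the list and places the results in sealed opaque envelopes. It then assigns the packing: "Postoperative care providers will prepare 5% lidocaine and placebo patches with patient numbers marked on the outer packaging". The next statement on roles is: "Patients, surgeons, anesthesia providers, outcome assessors, and statisticians will be blinded to group allocation". Postoperative care providers are not in it.

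Section 2.8 says of the envelopes that "these envelopes will only be opened after the study is completed". It adds three safeguards:

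- a matched placebo: "The placebo group will apply a placebo patch, identical in appearance and packaging to the actual medication patch";
- separation of those who apply the patches: "The patches will be applied by medical professionals who are not involved in patient recruitment or data collection";
- a general statement: "To maintain blinding, both patients and researchers will remain unaware of group assignments".

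Section 2.14 says: "The DMC will oversee and retain all data related to randomization until the designated time for unblinding". Section 2.15 routes emergency unblinding through the DMC as well.

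On the outcomes that ward staff could touch, section 2.9 describes a fixed sufentanil dose when a patient reports an NRS score of 4 or higher, in the PACU or later in the hospital stay. The 5 μg dose "of sufentanil was administered for analgesia, and the total dosage was recorded". It does not name who responds to the report or gives the dose. Section 2.5 lists sufentanil consumption, need for rescue analgesia, PACU stay and hospital stay among the secondary outcomes.

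**The concern.** Whoever decides which product goes into a numbered pack must either know the arm or work from coded stock. The article gives that task to a role whose title implies patient care, does not list that role as blinded, and describes no coded stock. It also closes every source of the allocation that it does name until the end of the trial. A reader cannot tell from these sections how the right patch reaches the right patient, or who knows the arm while patients are being treated.

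What is at stake is the blinding of the acute outcomes that pass through staff hands. A nurse or doctor who knows the arm may ask about pain more or less often, or act more or less quickly on a report. The Discussion names lower opioid consumption among the expected findings, so these secondary outcomes will carry weight in interpretation.

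**Working it through.** No arithmetic applies; the check sets the sections side by side.

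**1. Does the task need the allocation?** Section 2.7 describes two products and packs marked with patient numbers. The arm is a function of the patient number through the randomization list. Filling a numbered pack therefore needs that link, unless the stock arrives already coded by number. Section 2.8 says the patches come from one manufacturer and look alike, but not that they are supplied pre-numbered.

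**2. When is it needed?** Section 2.8 and Table 1 put the first patch on the day before surgery and the others on postoperative days 1 to 3. The link is thus used during the trial, for every patient.

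**3. Which sources are open then?**

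| Source | Section | Available during the trial? |
|---|---|---|
| Sealed envelopes | 2.8 | No, opened only at the end |
| Randomization data | 2.14 | Retained by the DMC until unblinding |
| Independent researcher's list | 2.7 | Generated there; no packing role stated |
| Pre-coded supply | none | Not mentioned |

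Steps 1 to 3 do not fit together. A task that needs the link is assigned to staff for whom no open source of the link is described.

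**4. Do the safeguards cover the preparers?**

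- The identical patch protects those who handle a finished pack, not a person who chooses its contents.
- The separation rule in section 2.8 names those who apply the patches. It says nothing expressly about those who prepare them, and for neither group does it exclude ward care or rescue dosing.
- The general statement covers patients and researchers. Whether clinical staff count as researchers is not said.

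**5. Which outcomes could be reached, if the preparers know the arm and also give ward care?**

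- *Need for rescue analgesia:* reachable. The trigger is the report of a blinded patient and the dose is fixed, but staff may differ in how often they ask and how they respond.
- *Sufentanil consumption:* partly reachable. The abstract describes postoperative sufentanil as patient-controlled, which leaves only the staff-given rescue part exposed.
- *Hospital stay:* possibly. Surgeons, who may influence discharge, are listed as blinded.
- *PACU stay:* not shown. Anesthesia providers are listed as blinded, and nothing gives this decision to the preparers.
- *Pain and sleep scores:* not shown. Patients and outcome assessors are listed as blinded.
- *WOMAC pain at 3 months:* not shown. It comes from blinded patients interviewed by blinded assessors, long after the last patch.

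**The case against.** The strongest reply is that the sealed envelopes and the DMC's custody of the list point to preparation without access to the allocation. On that reading the stock is coded in advance, ward staff only handle numbered packs, and nobody near the patient knows the arm. Packing details also commonly sit in a full protocol or pharmacy manual that a journal article condenses. Nor does the article say that preparers and appliers are different people; if they are the same, the bar on data collection in section 2.8 covers them too.

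Part of this stands. Coded supply is compatible with the text, so it would go too far to conclude that an unblinded list must be in the hands of the care team. A reader might also infer that the double-blind claim fails, or that all the acute secondary outcomes are compromised. The documents do not support either. No section says that the preparers give rescue doses or decide discharge, and patients, surgeons, anesthesia providers and assessors are listed as blinded.

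What does not stand is the idea that this is mere condensation. The article does not leave packing out. It states who does it, omits that role from the blinded list, and makes two custody statements that leave the task without a source. Coded supply would resolve the conflict, but it is stated nowhere. Even if preparers and appliers are the same people, a bar on recruitment and data collection is not a bar on giving care or rescue analgesia.

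**Conclusion.** The defect is in stated text. Section 2.7 gives an allocation-dependent task to a role outside its own blinded list, and sections 2.8 and 2.14 close the sources that the task would need. As written, the procedure either unblinds a patient-care role or cannot be carried out.

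The consequence is possible, not established. It rests on two assumptions that the article neither states nor excludes: that the preparers learn the arm, and that they also give postoperative care. If both hold, the exposure is limited to staff-given rescue analgesia, the rescue part of sufentanil consumption, and possibly hospital stay. The document gives no basis for a numerical size or direction of bias. The case for change is that the correction costs little and removes a doubt about outcomes the trial intends to interpret.

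**What to change.** 1. In section 2.7, move preparation to the independent researcher who already generates the list, or to the manufacturer. All patches for each patient are packed and numbered before delivery to the ward.
2. State that whoever holds the allocation during the trial has no role in patient care, rescue dosing or outcome recording.
3. Add postoperative care providers to the blinded roles in section 2.7.
4. Reconcile sections 2.7, 2.8 and 2.14 so that they agree on who holds the allocation during the trial, in what form, and until when. If the supply is already pre-coded, say so; that, together with item 3, would largely settle the point.

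The cost is a few sentences and one reassigned packing task. No extra patients are needed, and the outcomes and analysis are unchanged. If patients have already been treated, the report should state who prepared the patches and whether those staff knew the allocation or gave rescue analgesia.
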